### Assessment and follow-up

Participants in both arms of the trial will be asked to attend the baseline, 6-week and 12-week postintervention assessment visits at the PR centre at MLI. Data will be collected by the study staff (medical doctor, nurse and physiotherapist). Table 1 shows all baseline and follow-up assessment data that will be collected during the trial, in accordance with a minimum recommended dataset for PR trials in LMIC.^16^

**Table 1 T1:** The table shows the assessment and follow-up schedule

Observation/Investigation	Screening/baseline assessments	Randomisation	12 weeks of study participation	
			Hospital based pulmonary rehab	Follow-up phase of homebased exercises
			End of 6 weeks of PR	End of 6 weeks of home exercises
Written informed consent	x	x		
Demographics	x	x		
Medical history	x	x		
Clinical exam	x	x		
Chest X-ray	x			
Spirometry		x		
MRC dyspnoea grade	x		x	x
Assess symptoms	x		x	x
Incremental Shuttle Walk Test	x		x	x
Endurance Shuttle Walk Test	x		x	x
Borg breathlessness scale	x		x	x
Mid Upper Arm Circumference	x		x	x
Sit-to-stand time	x		x	x
COPD Assessment Test		x	x	x
Clinical COPD Questionnaire		x	x	x
Patient Health Questionnaire		x	x	x
HADS		x	x	x
WPAI		x	x	x
Physical Activity (Actigraph monitor)		x	x	x
Cost/benefit analysis		x	x	x
EQ-5D-5L Questionnaire		x	x	x

COPD, chronic obstructive pulmonary disease; EQ-5D-5L, European Quality of Life 5-Dimensions; HADS, Hospital Anxiety and Depression Scale; MRC, Medical Research Council; WPAI, Work Productivity and Activity Impairment.

### Study procedures

During the screening visit, prospective participants will undergo clinical examination, MRC dyspnoea grading, sputum examination using Xpert MTB/RIF assay and a frontal chest radiograph. In addition, demographic, socioeconomic, medical and clinical history (including respiratory symptoms and exposure history to cigarettes and biomass) will be collected using a standardised questionnaire. At the randomisation visit, spirometry will be performed using American Thoracic Society and European Respiratory Society guidelines.^17^

### Sample size

The study will be powered to detect a 35 m difference in the ISWT measured at baseline and after completion of PR.^18^ Assuming that ISWT follows an approximately normal distribution, a power calculation based on a paired t-test was performed. Based on a trial sample size of 40 participants in each of the treatment and control groups, a two-sided 5% significance level and a statistical power of 80%, the clinically important change in ISWT of 35 m will also be statistically significant. Our recent feasibility study^15^ was used to obtain an estimate of the pooled SD for the power calculation. Conservatively assuming up to 30% losts to follow-up at 6 weeks, a total of 114 participants are required to be recruited and randomised (1:1) to each arm (PR: 57 participants or waiting list: 57 participants). Using the 70% ineligibility rate during screening from the feasibility study, we will need to screen approximately 543 PTBLD patients.

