### Data analysis

All randomised participants will be included in the intention to treat analysis population. The primary efficacy analysis will be based on both per protocol and modified intention-to-treat populations. For the primary analysis, the differences in the primary outcome (walking distance on the ISWT) with the corresponding two-sided 95% CI and p value will be estimated using a stratified analysis; a p<0.05 will be the measure for statistical significance. Predictive analytics software (SPSS^16^) will be used to analyse the data. Continuous data will be presented as mean and SD or median and IQRs, while categorical data will be presented as frequencies and percentages. All data will be assessed for normality and appropriate parametric and non-parametric tests will be used. Categorical variables between the two treatment groups will be compared using χ^2^ and Fisher’s exact test as appropriate. Continuous variables will be compared using t-test for normally distributed data and Mann-Whitney-U test for non-normally distributed data. Any baseline differences will be adjusted for. Both intention-to-treat and per-protocol analyses will be conducted after imputing any missing data. There will be no formal interim analysis of data. The final analysis will be performed when all the 114 participants have completed the last study related visit or previously withdrawn from the trial. We will fit linear mixed models for both per-protocol and intention-to-treat analyses.

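### The sample size is justified by a paired pre/post t-test, but the trial compares two independent arms, so the named method does not support the stated 80% power for 35 m

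*Protocol article*

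**What the plan says.** In the protocol article, the Sample size section sets the target as a pre/post quantity: "The study will be powered to detect a 35 m difference in the ISWT measured at baseline and after completion of PR". It names the method: "Assuming that ISWT follows an approximately normal distribution, a power calculation based on a paired t-test was performed". The group size follows ("Based on a trial sample size of 40 participants in each of the treatment and control groups"), with "a two-sided 5% significance level and a statistical power of 80" per cent. The feasibility study "was used to obtain an estimate of the pooled SD for the power calculation". The value of that SD is not printed, nor whether it refers to walking distance or to within-person change. Allowing for up to 30% loss at 6 weeks, the total becomes 114, or 57 per arm.

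The rest of the article describes a between-arm trial. Study design and Randomisation set out 1:1 allocation to rehabilitation or waiting-list usual care. Data analysis plans a difference in ISWT distance with a 95% CI from a stratified analysis, adjustment for baseline differences, and linear mixed models. For continuous data in general it says: "Continuous variables will be compared using t-test for normally distributed data and Mann-Whitney-U test for non-normally distributed data". No section describes matched pairs or makes a paired test the primary comparison.

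**The concern.** A paired t-test asks whether the mean change within one group differs from zero. The trial asks whether mean change differs between two separate groups. The second question carries the sampling error of both arms. With equal arm sizes and the same SD of change, the variance of the contrast is twice that of a single arm's mean change. Power computed for the first question therefore does not carry over to the second.

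The 35 m target has the same problem. The sample size and primary outcome sections define it as a change from before to after the intervention, not as a difference between arms. Change in the rehabilitation arm also includes whatever change the usual care given to both arms would produce.

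The article lists being fully powered among the study's strengths. If the power for the between-arm comparison is well below 80%, that statement is wrong, and a non-significant result would be weaker evidence against benefit than readers would assume.

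**Working it through.** **Inputs from the Sample size section:** target 35 m; two-sided alpha 0.05; power 80%; 40 analysed per group; up to 30% loss. The SD is not stated.

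**Step 1: the plan's own figures.** The loss allowance reproduces: 80 / 0.70 = 114.3, against 114 stated. The figure of 40 per group cannot be reproduced forwards without the SD, so the SD is back-solved under each reading. Power is from the noncentral t distribution; d is the target divided by the SD.

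**Step 2: paired test as written, 40 pairs.**
- 80% power with 39 degrees of freedom needs d = 0.454.
- Implied SD of change = 35 / 0.454 = 77.0 m. The normal approximation, 35 × √40 / (1.960 + 0.842), gives 79.0 m.

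**Step 3: two-sample test, 40 per arm.**
- 80% power with 78 degrees of freedom needs d = 0.634.
- Implied SD = 35 / 0.634 = 55.2 m.

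**Step 4: the between-arm comparison if the SD of change is 77.0 m.**
- Standard error = 77.0 × √(2/40) = 17.2 m.
- Noncentrality = 35 / 17.2 = 2.03, where 80% power needs about 2.84.
- Power = 51.9%.
- Difference detectable with 80% power = 0.634 × 77.0 = 48.9 m.
- With no loss (57 per arm), power = 67%.
- About 77 analysed per arm would be needed for 80% (normal formula with SD 79.0 m: 81).

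**Step 5: range over the SD of change** (unadjusted two-sample t, 40 per arm, 35 m):

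| SD of change (m) | 55 | 60 | 65 | 70 | 77 |
|---|---|---|---|---|---|
| Power | 80% | 73% | 66% | 60% | 52% |

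**Step 6: if 77 m is instead the SD of raw distance.** Then SD of change = 77.0 × √(2(1 − ρ)), where ρ is the baseline-to-follow-up correlation. The article does not give ρ, so the values below are assumptions.

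| ρ | SD of change (m) | Power on change scores |
|---|---|---|
| 0.5 | 77.0 | 52% |
| 0.7 | 59.7 | 74% |
| 0.75 | 54.5 | 81% |
| 0.8 | 48.7 | 89% |

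Below ρ = 0.5, power falls under 52%.

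**Step 7: baseline adjustment.** The residual SD is the raw SD × √(1 − ρ²). With a raw SD of 77.0 m and ρ = 0.5 (so that the SD of change is also 77.0 m), this is 66.7 m, and power at 40 per arm is 64%.

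**The case against.** The strongest reply is that only the label is wrong. An SD described as pooled, and 40 in each of two named groups, is how one reports a two-sample calculation. On that reading the SD is about 55 m, 80% power is right, and one word needs changing. This stands as a possibility: the article does not let a reader exclude it. It does not remove the mismatch, because the named test would then be false.

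Second, 52% is not a figure from the article. It requires that 40 pairs were used, that the SD is of change, and that the analysis is unadjusted. Data analysis plans mixed models and adjustment for baseline differences, and the 30% loss is described as conservative. All of this stands, and it is why 52% can serve only as an illustration.

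Two stronger readings are tempting and are not supported:

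- A reader might infer that the statement "the clinically important change in ISWT of 35 m will also be statistically significant" confuses power with certainty and is a separate error. Read as being about an observed difference, it is true in both scenarios. The smallest significant between-arm difference at 40 per arm is 1.991 × 77.0 × √(2/40) = 34.3 m in one and 1.991 × 55.2 × √(2/40) = 24.6 m in the other, both below 35 m. The same sentence states the 80% power. The phrasing is loose, no more.
- A reader might infer that a learning effect on the walk test invalidates the pre/post target. The ISWT section provides a practice walk to deal with this, so the point is at least partly met.

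**Conclusion.** The concern holds as a mismatch between the sizing method and the primary comparison. The article bases 80% power at 40 per group on a paired within-person test, while its design and analysis sections call for a comparison of two independent arms, and nothing in it reconciles the two. Either the stated power or the named method is incorrect.

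How much power is lost is not established. Depending on which reading is true, power for 35 m is about 52% (paired test with 40 pairs, SD of change 77 m, unadjusted analysis, 30% loss) or 80% as stated (mislabelled two-sample calculation, SD 55 m). Intermediate or higher values follow if the SD is of raw distance with correlation above 0.5, if the analysis adjusts for baseline, or if loss is lower. A reader might infer that the trial has only about even odds of detecting its target. The article does not support that conclusion, because it does not state the SD on which it would depend.

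**What to change.** Replace the paired calculation in the Sample size section with a two-sample calculation, preferably adjusted for baseline, for the between-arm difference in ISWT change at 6 weeks. In it:

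- state the SD taken from the feasibility study and whether it is the SD of distance or of within-person change; if of distance, or if baseline adjustment is assumed, state the correlation used;
- define 35 m as a difference between arms;
- report the power for 35 m and the difference detectable with 80% power, both at 40 analysed per arm.

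If a two-sample formula was in fact used, correct the name of the test and print the SD.

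The cost is a rewritten paragraph and one recalculation from data the sponsor already has. Enrolment need not change. The drawback is that the stated power may fall or the detectable difference may rise, in which case the description of the trial as fully powered would need to be revised to match.

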### Blinding (masking)

Due to the nature of PR, it will not be possible to blind participants to their group allocation but participants will be asked not to reveal their group during the follow-up assessments. The participant and treating clinician will be aware of treatment allocation, however, the outcome measures will be performed by staff blinded to treatment allocation and the ISWT (primary outcome) will be prioritised to reduce the risk of un-blinding. Any episodes of unblinding will be documented and reported.

### Treatment arms

#### Usual care (control arm)

The participants in the waiting-list (control) arm will receive usual care and will be offered PR after completing 12 weeks of follow-up. There are currently no guidelines for the clinical management of PTBLD both locally and internationally. Usual care will be optimised where possible and will include the following: frontal chest radiograph, spirometry to screen for airway diseases, inhalational therapies for airway disease amenable to treatment (where appropriate), antibiotic and systemic glucocorticoid therapy for infective exacerbations (where appropriate), and verbal advice to quit smoking and reduce exposure to biomass smoke. According to local practice, all post-TB patients with significant postbronchodilator response on Spirometry (at least 12% and 200mls increase in forced expiratory volume in 1 s (FEV1)) are managed with a combination of inhaled corticosteroids and long-acting beta-agonists, while those with fixed airflow obstruction (postbronchodilator FEV1/forced vital capacity ratio of less than 0.70) are managed with long acting bronchodilators. PR will be offered as an adjunctive non-pharmacological treatment as recommended by international guidelines.^19^

#### PR (trial intervention arm)

In addition to usual care described above, participants in the intervention arm will receive PR. PR will consist of a 6-week programme offered to a group of up to 12 participants, with sessions occurring twice weekly for at least 2 hours (approximately 1 hour for education and 1 hour for exercise).

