### COVID-19 provisions

Modifications will be made to the delivery of the PR programme due to the COVID-19 pandemic. The PR room will be reorganised to allow for social distancing (minimum 2 m) for both study staff and study participants. The maximum number of participants participating in the PR session will be reduced from 12 to 8 to ensure social distancing between participants. Before accessing the PR room, all participants and staff will be required to undergo temperature measurement using a hand-held non-contact thermometer, wash hands with soap or alcohol-based hand sanitiser. All participants will be provided with face masks during PR sessions. All surfaces inside the PR room will be disinfected before and after every PR session. PR sessions will be conducted in the morning hours to allow participants travel back home in time before the evening rush hour and the standard operating procedure for data collection will be modified ensure 2-metre distancing between the study staff and study participant. Study participants will undergo COVID-19 testing before starting PR and as needed during the hospital based sessions. All study staff will be required to wear N95 masks at all times and will undergo COVID-19 training with emphasis on infection prevention and control, and screening study participants for signs and symptoms of the disease.

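### The sample size makes no allowance for clustering by PR class in the intervention arm, and the analysis section does not mention class; if the class ICC is positive, power is below 80% and an analysis that ignores class gives too narrow an interval

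*Protocol article*

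**What the plan says.** All places are in the protocol article.

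- **Delivery, PR arm** (PR (trial intervention arm)): "PR will consist of a 6-week programme offered to a group of up to 12 participants", with two sessions a week.
- **Delivery, revised** (COVID-19 provisions): "The maximum number of participants participating in the PR session will be reduced from 12 to 8".
- **Control arm** (Usual care (control arm)): these participants "will receive usual care and will be offered PR after completing 12 weeks of follow-up". They therefore attend no class before the 6-week primary assessment.
- **Randomisation**: individual, 1:1.
- **Sample size**: the trial is "powered to detect a 35 m difference in the ISWT measured at baseline and after completion of PR", and "a power calculation based on a paired t-test was performed". The figures given are 40 analysed per arm, two-sided 5% significance, 80% power, and up to 30% loss at 6 weeks, leading to 114 randomised. The SD is not printed, and there is no ICC or design effect.
- **Data analysis**: "Continuous variables will be compared using t-test for normally distributed data and Mann-Whitney-U test for non-normally distributed data". The section also plans a stratified analysis without naming the strata, and linear mixed models without naming the random effects. PR class appears in neither.

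**The concern.** People who train in the same class for 6 weeks share group warm-ups, education sessions and peer support. Their changes in ISWT distance may therefore be more alike than those of participants in different classes. Controls have no such grouping before 12 weeks, so any correlation of this kind inflates the variance of the PR-arm mean only.

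A t-test or Mann-Whitney test treats all participants as independent. With positive correlation within classes, it understates the standard error of the primary difference, so the 95% interval covers less often than stated and the false-positive rate exceeds 5%. A valid analysis would have less power than the 80% quoted. This matters for a trial that its strengths and limitations box describes as fully powered.

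**Working it through.** **1. The plan's own figure.** Inputs: 40 analysed per arm and 30% loss (Sample size). 80 / (1 − 0.30) = 114.3, close to the stated 114; as a cross-check, 57 × 0.7 = 39.9 per arm. The whole inflation from 80 to 114 is spent on dropout, and nothing is left for clustering. The 40 per arm cannot be reproduced, because the SD is not printed. Taken as a two-sample comparison at 80% power, it implies an SD of change of 35 / [(1.960 + 0.842) × √(2/40)] = 55.9 m. That SD cancels in the steps below.

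**2. Number and size of classes.** If classes are full and contain only trial participants from the PR arm, 57 / 12 = 4.75 gives 5 classes and 57 / 8 = 7.1 gives 8. After 30% loss, the number analysed per class (m) is 8 × 0.7 = 5.6, or 12 × 0.7 = 8.4.

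**3. Formulas.** With clustering in the PR arm only and equal analysed numbers:

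- PR-arm design effect: D = 1 + (m − 1) × ICC
- Variance ratio of the arm difference: V = (1 + D) / 2
- Power of a valid analysis: Φ(2.802 / √V − 1.960), set to give 80% when the ICC is 0
- Type I error if class is ignored: 2 × [1 − Φ(1.960 / √V)]

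Worked example, m = 5.6 and ICC 0.05: D = 1 + 4.6 × 0.05 = 1.23 and V = 1.115, so √V = 1.056. Power = Φ(2.653 − 1.960) = Φ(0.693) = 75.6%. Type I error = 2 × [1 − Φ(1.856)] = 6.3%.

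**4. Results.** The ICC values are assumptions.

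| Analysed per class | ICC | D | V | SE multiplier √V | Power | Type I error, class ignored |
|---|---|---|---|---|---|---|
| 5.6 (maximum 8) | 0.01 | 1.046 | 1.023 | 1.01 | 79.1% | 5.3% |
| 5.6 | 0.02 | 1.092 | 1.046 | 1.02 | 78.2% | 5.5% |
| 5.6 | 0.05 | 1.230 | 1.115 | 1.06 | 75.6% | 6.3% |
| 5.6 | 0.10 | 1.460 | 1.230 | 1.11 | 71.4% | 7.7% |
| 8.4 (maximum 12) | 0.02 | 1.148 | 1.074 | 1.04 | 77.1% | 5.9% |
| 8.4 | 0.05 | 1.370 | 1.185 | 1.09 | 73.0% | 7.2% |
| 8.4 | 0.10 | 1.740 | 1.370 | 1.17 | 66.8% | 9.4% |

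At ICC 0 nothing changes. A simulation of the two-sample t-test that ignores class (40,000 runs per setting, 40 per arm, up to 6 analysed per class) gave type I errors of 5.3%, 6.5% and 7.8% at ICC 0.01, 0.05 and 0.10, in line with the formula. The powers use a normal approximation; small-sample degrees of freedom would lower them a little further.

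**5. How well class variance can be estimated.** Take 7 classes of 5.6 (about 40 analysed). The ANOVA estimate of class variance is zero or negative when an F variable on 6 and 7 × 4.6 = 32.2 degrees of freedom falls below (1 − ICC) / D. That probability is about 49% at ICC 0.02 (threshold 0.98 / 1.092 = 0.897) and about 40% at ICC 0.05 (0.95 / 1.23 = 0.772).

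**The case against.** A reader might infer that the planned analysis definitely treats everyone as independent and that the interval therefore is too narrow. The document does not support either step. The linear mixed models are named without any random effects, so a class term is neither stated nor excluded, and an article may leave that detail to the SAP. The interval is too narrow only if the class ICC is positive and class is left out, and no ICC is given. Both points stand, and the conclusion is conditional for that reason.

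There are also grounds to expect a small ICC. One site and one trained PR team are described, so differences between staff need not create differences between classes. Controls are randomised concurrently, so calendar period is not peculiar to the PR arm. Walking is prescribed individually, the education programme is fixed, and the outcome is a change on an externally paced test measured by blinded staff. These features favour the lower part of the range but do not make the ICC zero: shared sessions and peer effects remain.

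The larger figures (V = 1.37, power 67%, type I error 9.4%) need full classes of 12, which the COVID-19 provisions replace with a maximum of 8. Both sizes are maxima. If waiting-list patients later join the same classes, the number of trial PR-arm participants per class would be smaller still.

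Finally, about 5 to 8 classes give weak information on class variance, so the remedy will often return a zero estimate. That limits the fix without removing the case for it.

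**Conclusion.** The concern holds conditionally. Two facts are fixed in the text: PR is given in classes in one arm only, and the sample size has no allowance for this. The analysis section names independence-based tests and does not mention class.

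At the current class maximum, with 5.6 analysed per class and an assumed ICC of 0.02 to 0.10, power is about 78% to 71% rather than 80%, and a test that ignores class has a type I error of about 5.5% to 7.7%. At ICC 0.01 the effect is negligible; if classes of 12 were run, both figures are worse. These sizes assume full, equal classes, 40 analysed per arm, and that 40 per arm would give 80% power for the between-arm comparison without clustering. The last assumption is itself uncertain, because the plan used a paired t-test; that is a separate and potentially larger issue.

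This is a worthwhile, inexpensive correction to the primary analysis, and not evidence that the trial's result will be invalid.

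**What to change.** 1. Record a class identifier for every PR participant as classes run; it is harder to reconstruct later.
2. In the linear mixed model already planned, add a random class effect in the PR arm only, with each control as its own cluster. Use Satterthwaite or Kenward-Roger degrees of freedom.
3. Name that model as the source of the primary between-arm estimate, interval and p value, in place of the t-test or Mann-Whitney test.
4. Restate power over a declared ICC range, for example 0.02 to 0.10, at the class sizes actually run. No further enrolment is proposed.

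**Cost:** one database field, one model term and a revised sample-size paragraph. The interval will be slightly wider. With about 5 to 8 classes the class variance is poorly estimated and may often be estimated as zero, in which case the model gives nearly the same answer as one without class, so protection is partial. The report should therefore give the estimated class variance and the number of classes next to the primary result.
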